### Cooperating centres and participants

Eligible institutions for delivering the interventions, i.e. experienced in dealing with the clientele at hand, were identified by systematically scanning comprehensive help provision and therapy guides, using existing online and offline lists and conducting an internet search. We also gathered data on their relevant activities in the area by sending out a questionnaire on their work with children from substance-affected families [41]. All participating centres signed cooperation contracts before delivering the programme and received financial incentives for their participation. As a number of facilities agreed to cooperate, but could not recruit enough participants to conduct the intervention, several efforts had to be made during the entire field phase to engage and train new cooperation partners. In the end, 27 cooperating out-patient counselling centres participated in the project. Centres were almost uniformly distributed across the country with at least one participating centre in nearly every federal state. Most of the centres were addiction aid facilities and only some were youth and family support services or other groups. Participating facilities recruit participants using their existing recruitment strategies as well as recruitment material provided by the research team (flyers, webpage, posters, newspaper advertisements). They conduct intake talks with children and parents, inform them about the content and goal of the programme and screen participating children for eligibility. Inclusion criteria for children are: (1) age at beginning of the programme between 8 and 12 years, in exceptions after careful screening between 7 and 13 years if developmental phase fits (2) current or recent (within the last year) substance misuse or dependency in at least one parent (3) children either live with the substance-affected parent or have regular contact with him or her (4) sufficient mastery of the German language both in children and parents to participate in assessments (5) informed written consent of the parents and the children. Children are excluded from the study if (1) they are diagnosed with or suspected of foetal alcohol spectrum disorder by recruiting staff due to extreme behavioral difficulties or if (2) they have received any kind of addiction-specific treatment relevant to the study goals up to six months prior to the intervention. Participating children and parents do not receive financial incentives for participating in the intervention, but they do receive a small compensation for participating in data collection (10€ per parent and questionnaire, a small present worth 2-3€ per child and interview).

### Data collection

Data are gathered at three points: At baseline, i.e. two weeks prior to intervention (t0), shortly after the intervention (t1) and six months after the intervention (t2). Data from the third measurement point is collected until the end of January 2012. To address the expected parental concerns about anonymity mentioned above and to avoid bias, we trained bachelor-level students of social and public health science from all over Germany to gather data. The students visited the families at all three measurement points and interviewed the children while providing parents with paper-and-pencil questionnaires. Interviewers were extensively trained in the specific challenges of surveying substance-affected families and are closely supervised to deal with problems that may come up. For example, even though a mother had been informed that this was a group programme on drug use and addiction, she refused to let an interviewer survey her child on this topic since she had not "told him yet". In cases like this, the interviewer called the researchers for immediate guidance. With regard to measurements, we used age-adequate standardised instruments, where possible, to assess our outcome variables. Children report on socio-demographic data, current parental substance use, stress level and coping strategies, self-worth, self-efficacy and satisfaction with the intervention, relationship quality with the parent, addiction-related knowledge and health-related quality of life. Parents (ideally both) or primary caregivers report on psychological stress, their own substance use, relationship quality with the child, sensitivity for children's needs, assertiveness regarding their own parenting competence, parenting style, child coping strategies and child behavior. An overview of measurements is given in Table 1. Interviewers are blind to condition at baseline and at t1, but not at t2 due to the fact that only the parents in the intervention condition participate in group sessions and are asked about them in t2.

**Table 1 T1:** Measures for children and parents

Target variable - CHILD	Measure
*Socio-demographic characteristics*	

*Self-concept/self-worth*	SPPC - Self Perception Profile for Children (German version) [51,52]

*Physical stress symptoms*	SSK - Fragebogen zur Erhebung von Stresserleben & Stressbewältigung im Kindesalter [53] Questionnaire for perception of stress and stress management in childhood Subscale: physical stress symptoms

*Quality of relationship between parent and child*	Own development: questions on a thermometer-scale in regard to closeness vs. distance and harmony vs. conflict

*Parental drug and addiction problems*	CAST 6 - German Children of Alcoholics Screening Test [54,55]

*Knowledge on alcohol, drugs, and substance use problems*	Own development

*Stress and coping*	SSKJ 3-8 - Fragebogen zur Erhebung von Stresserleben & Stressbewältigung im Kindes- und Jugendalter [56] Questionnaire for perception of stress and stress management in childhood and adolescence

*Mental distress caused by parental substance use*	Own development

*Expectations of self-efficacy*	WIRKALL-r - Psychometrische Skala zur Allgemeinen Selbstwirksamkeitserwartung (SWE) - für Kinder adaptierte Version [57,58] Psychometric scale for general expectation of self-efficacy - adapted version for children Adaptation of a scale used for measuring self-efficacy in the family [59,60]

*Health-related quality of life*	KIDSCREEN-27 - Health related quality of life questionnaire for children and young people and their parents [61,62]

**Target variable - PARENT**	**Measure**

*Socio-demographic characteristics*	

*Psychological stress*	Symptom checklist SCL-27-plus [63]

*Parental substance use problems*	Alcohol Use Disorders Identification Test (AUDIT) [64,65]

*Parental use of further substance-related aid*	Own development

*Parental sensitivity for the effects of substance use problems on children and children's need*	Own development

*General parenting behaviour*	ZKE-E - Kurzfragebogen zur Erfassung elterlicher Erziehungshaltungen [66] Brief questionnaire for perception of child-raising behaviour (parent version)

*Quality of relationship between parents and child*	Own development: questions on a thermometer-scale in regard to closeness vs. distance and harmony vs. conflict

*Self-confidence in parenting skills*	Fragebogen zum Kompetenzgefühl von Eltern (FKE) [67] Questionnaire for parental feelings of competence

*Child behavioural difficulties*	SDQ-D-German (Strength and Difficulties Questionnaire, German version) [68,69]

*Stress management strategies of* *the child*	SSKJ 3-8 - Fragebogen zur Erhebung von Stresserleben & Stressbewältigung im Kindes- und Jugendalter [56] Questionnaire for perception of stress and stress management in childhood and adolescence

Besides gathering outcome evaluation data on the effectiveness of the TRAMPOLINE programme, process evaluation data is also collected. Course instructors in the participating centres complete an extensive documentation on relevant variables (adherence, interaction with the group, possible disturbances) after each child and parent session. Also, the instructors are required to conduct visual recordings of two out of the nine child sessions chosen by the research team. Children and parents evaluate each session they participate in directly after the session is over. In addition, course instructors and institute managers complete questionnaires on relevant characteristics such as structural data on their institute or professional background. These data will be used to analyse the quality of manual adherence and to identify possible influencing factors such as instructor qualification or group atmosphere.

### Statistical analyses

The sample size for our study is based on a power analysis for detecting small effect sizes. In general, existing literature shows that medium effect sizes can occur, but these studies utilise wait-list controls so that effects may be stronger than in the study at hand. When using a two-sided test at alpha = 0.05 and a power of (1-beta) = 0.80, a total sample of at least N = 200 is required [70]. This takes a worst case scenario of 30% loss-to-follow-up after randomisation into account. Data will be analysed in a 2 × 2 ANCOVA design and in accordance with the per-protocol principle, since we are primarily interested in the effect of the programme on those children that actually participated in the programme from start to finish. In addition, in secondary analyses we will examine the data following the intention-to-treat principle to identify possible effects of attrition. A dropout analysis will be conducted. Missing data will be imputed. The ANCOVA approach will be employed for baseline-adjusted analyses. For computations, the SPSS standards software will be used.

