The limitations of the study must also be mentioned: Due to the volatile nature of the families we target, it may be difficult to motivate them to participate in follow-up assessments. Also, many substance-affected parents will not let their children participate in the programme, thus creating a selection effect in the sample from the start. Moreover, we view the age range of the participating children as substantial and it must be seen if the programme will be beneficial for all age groups. For example, some exercises require writing and reading skills, and trainers have reported that especially younger children still need quite a lot of help in this area. Furthermore, it would be desirable to compare the effects of the programme with a naturalistic sample of children from substance-affected families not receiving any intervention. It was attempted to recruit this sample, but it quickly became clear that this recruitment challenge would exceed our resources. We also expect that attrition during the interventions will be substantial, because families view a weekly participation of their children in such a programme as a high demand on their daily routine. We try to handle this problem by encouraging our cooperating centres to contact the families if a child does not show up for a session and to support the families in any way they can regarding transportation and logistics. The reasons for dropouts are to be documented and will be analysed within the process evaluation. We hope to find out whether dropouts are due more to reasons such as time constraints in the family or rather to dissatisfaction with aspects of the programme or both. This analysis can possibly provide insights into the acceptance of the programme.

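### N = 200 with 30% loss does not give 80% power for a conventional small between-group effect, and the article does not say which small effect it means

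*Protocol article*

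**What the plan says.** The Statistical analyses section opens with the target: "The sample size for our study is based on a power analysis for detecting small effect sizes". It sets this against earlier research: "existing literature shows that medium effect sizes can occur, but these studies utilise wait-list controls so that effects may be stronger" than in this trial. The error rates follow ("When using a two-sided test at alpha = 0.05 and a power of (1-beta) = 0.80"), then the result, "a total sample of at least N = 200 is required", and the allowance for loss: "This takes a worst case scenario of 30% loss-to-follow-up after randomisation into account".

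The planned analysis is described in the same paragraph: "Data will be analysed in a 2 × 2 ANCOVA design and in accordance with the per-protocol principle", and "The ANCOVA approach will be employed for baseline-adjusted analyses". The Trial design section reports 218 children at baseline, randomised individually within each centre.

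The article gives no numerical effect size, effect metric, standard deviation or baseline-outcome correlation, and does not name the test behind the calculation. It gives a literature reference for the calculation.

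**The concern.** The paragraph makes one joint claim: small effect, two-sided 5% test, 80% power, 200 randomised, 30% loss already absorbed. Small is contrasted with the medium effects of wait-list studies, so the natural reading is the conventional graded one, d = 0.20 for a difference between two arms. On that reading the number is too small by a factor of more than five.

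The claim matters because of the comparator. The control is an active play group of equal duration, and the authors themselves expect effects that may be weaker than against a wait list, so small effects are the ones in play. A reader who takes the statement at face value could treat a non-significant result as evidence against a small effect that the trial had a low chance of detecting. The article does not draw that inference, but its power statement invites it.

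**Working it through.** **Inputs from the article.** Two-sided alpha 0.05; power 0.80; N = 200; 30% loss, so 200 × 0.70 = 140 analysed; 218 enrolled, so 218 × 0.70 = 152.6, about 153 analysed.

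**Assumptions.** 1:1 allocation (ratio not stated); d = 0.20 as the conventional small effect, with larger values shown; baseline-outcome correlation r from 0 to about 0.9 (not stated). Results use the noncentral t distribution. The normal formulas below show where they come from.

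**1. Trying to reproduce 200 for d = 0.20, unadjusted.** Total N = 4(1.960 + 0.842)²/d² = 4 × 7.85/0.04 = 785, or 786 in two equal arms (788 with t). Dividing by 0.70 gives 1,126 randomised. The stated 200 is not reproduced.

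**2. Power of the stated plan at d = 0.20.** With 140 analysed the noncentrality is 0.20/√(4/140) = 1.183, and power is Φ(1.183 − 1.960), about 22%. Baseline adjustment divides the noncentrality by √(1 − r²):

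| r (assumed) | Power at d = 0.20, 140 analysed | Detectable d, 140 analysed | Detectable d, 153 analysed |
|---|---|---|---|
| 0 | 22% | 0.48 | 0.46 |
| 0.5 | 27% | 0.41 | 0.39–0.40 (0.395) |
| 0.7 | 38% | 0.34 | 0.33 |
| 0.8 | 50% | 0.29 | 0.27 |

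Detectable d is the effect found with 80% power. Unadjusted, it is 2.802 × √(4/140) = 0.474 (0.477 with t). Multiplying by √(1 − 0.25) = 0.866 gives 0.413, and by √(1 − 0.49) = 0.714 gives 0.341.

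**3. Correlation needed for the claim at d = 0.20.** 1 − r² = (0.20/0.477)² = 0.176, so r = √0.824, about 0.91. With 153 analysed it is about 0.90.

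**4. Enrolment above 200 does not change the picture.** With 153 analysed, power at d = 0.20 is 23% unadjusted, 29% at r = 0.5 and 41% at r = 0.7. Even if all 218 were analysed, unadjusted power would be 31%.

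**5. Which calculations do give 200?**

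- Two-sample t test, d = 0.40, no loss: 200 analysed.
- Two-sample t test, d = 0.48, loss included: 140 analysed, 140/0.70 = 200.
- Group-by-time interaction with two time points, f = 0.10, noncentrality f²·N·2/(1 − r). With N = 140 and r = 0.65 this is 0.01 × 140 × 2/0.35 = 8.0, power 0.80, so 200 with loss included. With N = 200 and r = 0.5 it is 0.01 × 200 × 2/0.5 = 8.0, again power 0.80, but with no loss.

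In the interaction metric, f = 0.10 means each cell departs by 0.10 SD. The difference between arms in pre-post change is therefore 4 × 0.10 = 0.40 SD. That carries the label small, but it is twice a conventional small difference between arms.

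**The case against.** The strongest defence is that the claim can be made coherent. An interaction test with Cohen's small f = 0.10 and a correlation of 0.65 gives 80% power at 140 analysed, exactly 200 after 30% loss. Small may also mean only below medium: with baseline-adjusted analysis of 140 children, d = 0.40 is reached at a correlation of about 0.54. The metric and correlation may stand in a fuller protocol or in the cited source.

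This stands to the extent that an arithmetic error is not proven. It does not rescue the sentence as printed: the test and correlation are not in the article, and both routes concern an effect of 0.40 SD, not 0.20. Leaving such details to a fuller document is ordinary. The finding rests on the positive claim about small effects.

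Two stronger readings are tempting and should be resisted.

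- **That 200 is the no-loss figure for d = 0.40, so the 30% was never added.** The article states no d, says expressly that loss was included, and 200 fits other inputs with loss included equally well.
- **That the trial really detects only d = 0.48.** That is the unadjusted figure for 200 randomised. The plan is baseline-adjusted and 218 were enrolled.

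Per-protocol exclusions could lower the analysed number further. The Discussion warns "We also expect that attrition during the interventions will be substantial", while the 30% is described as loss to follow-up. But children who leave the programme may largely be those lost to follow-up, and nothing shows that the two losses add up.

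**Conclusion.** The concern holds in limited form. For a conventional small difference between arms, the stated 80% power is not delivered: it is about 22% unadjusted and 27% to 38% at assumed correlations of 0.5 to 0.7, for 140 analysed. Only a correlation near 0.91 would make the statement true. On the actual enrolment with 30% loss, the trial has 80% power for d of about 0.46 unadjusted, or about 0.40 to 0.33 adjusted at those correlations.

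These figures assume 1:1 allocation and d = 0.20 as the meaning of small. They make no allowance for clustering within groups or for per-protocol exclusions beyond the 30%; either would raise the detectable effect. The origin of 200 remains undetermined, so this is a power claim that its stated inputs do not support, not a demonstrated miscalculation.

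**What to change.** Leave enrolment as it is and rewrite the sample-size statement:

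- State that 218 enrolled with 30% loss, about 153 analysed, gives 80% power (two-sided alpha 0.05) for d of about 0.46 unadjusted, or about 0.40 to 0.33 with baseline adjustment at assumed correlations of 0.5 to 0.7, before any clustering or further per-protocol exclusions.
- Name the effect metric, the test and the correlation used. If the calculation was an interaction with f = 0.10, say that this is a 0.40 SD difference in change.
- Remove the unqualified claim of power for small effects.
- Specify that a non-significant result will be interpreted through its confidence interval and will not be taken as excluding d = 0.20.

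The cost is a few sentences and a less favourable stated detectable effect. Design, recruitment and data collection are untouched.

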## Methods/Design

### Trial design

The effectiveness of the nine-session group programme TRAMPOLINE for children from substance-affected families will be tested in a multicentre randomised controlled trial. Out-patient counselling facilities across the nation were chosen as project facilities since they currently have primary access to the target group in Germany. In total, 27 facilities from different settings (rural/urban, Northern/Southern/Eastern/Western regions of the country) deliver interventions. The group programme TRAMPOLINE was designed and manualised in 2008/2009 during the first phase of the 3.5-year project. It is specifically geared to the issues and needs of children and parents in substance-affected families. The control condition was originally planned as a "Treatment as usual (TAU)" group, until it became clear that TAU varies strongly between facilities due to their heterogeneous approaches and is in many cases hardly comparable to a structured group programme (e.g., individual counselling sessions over many months). Thus, to ensure comparability, we designed a group programme with the same duration that is not addiction-specific (both interventions are described below) and that functions as control group setting. This will enable us to identify effects of TRAMPOLINE that go above and beyond a general group setting with effects resulting from variables such as trainer attention or social networking. We view this as quite a rigorous test, given the fact that the common design of many international studies of this kind utilises wait-list controls and thus compares "intervention" with "no intervention" [35]. At baseline N = 218 children aged 7-13 years have entered the programme. Although the programme is designed for 8 to 12 year-olds, execeptions were made after screening for children whose developmental status fits in with this age group, allowing for the occasional 7 to 13 year-old. For each project centre, our research institute randomly assigned participating children either to the intervention condition or to the control condition. At the time this manuscript is drafted, the field phase is ongoing, with baseline data collection already completed.

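### The stated ANCOVA names no term for the group in which children are treated; if outcomes correlate within groups, its standard error is likely too small and its type I error likely above 5%.

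*Protocol article*

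**What the plan says.** **Analysis.** Protocol article, Statistical analyses: "Data will be analysed in a 2 × 2 ANCOVA design". The same paragraph adds baseline adjustment, a per-protocol primary analysis, an intention-to-treat secondary analysis and imputation of missing data. It does not name the two factors of the design. It mentions no group term, centre term, random effect or cluster-robust error.

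**Allocation.** Trial design: "For each project centre, our research institute randomly assigned participating children either to the intervention condition or to the control condition". The number of centres is given there too: "In total, 27 facilities from different settings". So the child is the unit of allocation and the centre is the stratum.

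**Delivery.** According to Trial design and Interventions, both conditions are manualised group programmes of equal length. The intervention has nine weekly sessions of 90 minutes. Quality assurance says that centre staff deliver both conditions and that at least two trainers are trained per centre.

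**Group influence.** Data collection says that the process data will serve, among other things, to "identify possible influencing factors such as instructor qualification or group atmosphere". This belongs to the process evaluation and is not carried into the outcome model.

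**Sample size.** Statistical analyses states: "a total sample of at least N = 200 is required". The one allowance described is for attrition: "This takes a worst case scenario of 30% loss-to-follow-up after randomisation into account".

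**The concern.** Children are randomised one by one but then treated together. For nine weeks those in a group share sessions, peers and leaders, so their outcomes may be more alike than those of children in different groups. Because each group sits wholly in one arm, a shared group effect does not cancel between arms. It adds to the variance of the difference between conditions. An ANCOVA on individual children does not see that variance and reports a standard error that is too small whenever the within-group correlation is positive and nothing offsets it.

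At stake is the test of the primary hypothesis on coping. A nominal p below 0.05 would overstate the evidence, and the confidence interval would be too narrow.

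The article treats such influences as possible. It plans to look for effects of group atmosphere and instructor qualification, and it justifies the active control by general effects of the group setting. That does not establish a correlation, but it makes an assumption of exactly zero hard to defend.

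**Working it through.** **1. The plan's own figure.** The article gives a two-sided alpha of 0.05, power of 0.80 and N = 200 with 30% loss included. It describes the target only as "based on a power analysis for detecting small effect sizes", so N = 200 cannot be reproduced uniquely. A standardised difference of 0.2 needs 786 children, and 0.4 needs 198, both without loss or clustering. The sample-size basis is a separate matter. Here it matters only that no allowance for clustering is described.

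**2. Inputs**
- From the documents: 218 children, 27 centres, two conditions, 30% loss, alpha 0.05 two-sided.
- Assumed: 1:1 allocation, one group per condition per centre, groups of equal size, and group ICC between 0.02 and 0.10. In the formula below, the ICC is the one that remains after baseline adjustment.

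**3. Group size.** 27 × 2 = 54 groups and 218/54 = 4.04, so m is about 4. After 30% loss spread evenly, 0.7 × 4.04 = 2.8.

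**4. Formulas.** Design effect DE = 1 + (m − 1) × ICC. Actual two-sided error of a test that ignores the groups = 2 × (1 − Φ(1.96/√DE)). Effective number of children = 218/DE.

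**5. Results for m = 4**

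| Group ICC | DE | Type I error | Effective number of 218 | True SE / reported SE (√DE) |
|---|---|---|---|---|
| 0.02 | 1.06 | 5.7% | 206 | 1.03 |
| 0.05 | 1.15 | 6.8% | 190 | 1.07 |
| 0.10 | 1.30 | 8.6% | 168 | 1.14 |

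After loss, with m = 2.8 and ICC 0.05: DE = 1 + 1.8 × 0.05 = 1.09; 1.96/√1.09 = 1.88; error about 6%.

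If groups were larger, with m = 6, the error would be 6.2%, 8.0% and 11.0% at the same three ICCs.

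**6. Adding centre effects, by simulation.** No true effect, 27 centres, two groups of 4 per centre (216 children), individual allocation within centre, 8,000 runs per setting. The simulation standard error is about 0.24 percentage points at 5%: √(0.05 × 0.95/8,000) = 0.0024.

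| Group ICC | Centre ICC | Plain ANCOVA | ANCOVA with centre factor only | Group means paired by centre |
|---|---|---|---|---|
| 0 | 0 | 5.2% | 5.2% | 5.3% |
| 0 | 0.05 | 4.7% | 5.1% | 5.2% |
| 0.02 | 0.05 | 5.2% | 5.8% | 5.0% |
| 0.05 | 0 | 6.8% | 7.0% | 5.1% |
| 0.05 | 0.05 | 6.4% | 7.5% | 5.2% |
| 0.10 | 0 | 8.2% | 8.9% | 4.9% |
| 0.01 | 0.10 | 4.2% | 5.5% | 4.9% |

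Three things follow. Shared groups raise the error. Leaving out centre, when children are allocated within centre, lowers it, because centre variance stays in the residual although it cancels from the contrast. A centre term alone removes that offset but leaves the group effect untreated. The analysis that takes the group as its unit stays near 5% throughout.

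**The case against.** **The two omissions pull in opposite directions.** A reader might infer that allocation within 27 centres is itself a source of excess false positives. It is not. With a centre effect only, the plain ANCOVA is conservative (4.7% at centre ICC 0.05), and the cost is precision. A small group effect beside a centre effect can leave the error near or below 5%. This objection stands, and the inflation must be attributed to shared groups alone.

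**The size is assumed.** A reader might also infer that the 5% rate is certainly breached. The documents give no ICC, group size or number of courses per centre, and the figure of 4 per group is a division, not a statement. Smaller groups, including those left after attrition, shrink the inflation. This stands too, so the claim has to be conditional.

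**Whole centres in one arm.** Someone might read the allocation sentence as sending each centre to a single condition, which would make clusters of about 8 and a larger inflation. The text says that children were assigned for each centre, to one condition or the other. That scenario has no support.

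**Trainers may serve both arms.** The article does not say that trainers differ by condition. If the same staff lead both groups in a centre, their effect is largely shared within the centre and cancels. What remains is the effect of the peers and of the group's own course, which does not cancel.

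**The article is a summary.** Further model terms are often left to an analysis plan. That lowers confidence, but it does not remove the point: the article names a model, and that model, applied as stated, does not match the stated delivery in groups.

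**Conclusion.** The concern holds in conditional form. The named ANCOVA has no term for the delivered group, while both arms are delivered in groups nested within condition. If the within-group correlation is material, the standard error of the primary contrast is likely too small and the type I error likely above 5%.

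With about 4 children per group, a group ICC of 0.02 to 0.10 and no centre effect, the error is about 5.7% to 8.6%. A centre effect lowers it, to about 5% at group ICC 0.02 with centre ICC 0.05. This is a moderate distortion, and the documents cannot settle its exact size. It merits correction because valid inference should not depend on an unmodelled centre effect happening to balance an unmodelled group effect. Severity: should be fixed. Confidence: moderate.

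**What to change.** In Statistical analyses, replace the plain ANCOVA with a linear mixed model of the outcome on condition and baseline score, with centre as a factor and a random intercept for the delivered group in both arms. Identify groups by centre, condition and course. Use Satterthwaite or Kenward-Roger degrees of freedom. With one group per condition in each of 27 centres, the contrast then rests on about 27 − 1 = 26 degrees of freedom. An analysis of baseline-adjusted group means paired by centre would be an acceptable equivalent. Adding centre alone would not be enough.

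Apply the same structure to the per-protocol and the intention-to-treat analyses, and report the estimated group ICC.

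**Cost.** Wording, plus slightly wider confidence intervals: by a factor of √1.15 = 1.07 at a group ICC of 0.05 with 4 per group, before the small-sample correction and before any precision regained by modelling centre. Centre is known from allocation, and group membership should be recoverable from the session documentation that instructors complete. When the article was written, only baseline collection was complete, so the change could be made before outcomes were analysed.
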